#### Statistical Methods

All analyses will follow an intention-to-treat approach and will be conducted using R (R Foundation for Statistical Computing). Statistical tests will be 2-tailed with a significance level of α=.05. Descriptive statistics will summarize sample characteristics. Baseline group differences will be assessed using Pearson chi-square tests for categorical variables and independent-samples *t* tests (or nonparametric equivalents) for continuous variables. Any variables showing systematic baseline imbalance will be considered as covariates in sensitivity analyses.

To evaluate the primary outcomes—changes from preexposure (T0) to immediate postexposure (T1) in EEG alpha power, cognitive performance (Meta Mind and Star Racer), and ASRS, we will implement linear mixed-effects models (LMMs) using the *lme4* package. Fixed effects will include exposure condition (real vs VR nature), diagnostic group (ADHD vs neurotypical), time (T0 vs T1, with T9 added where relevant to examine short-term maintenance), and their interactions. Participant will be entered as a random intercept; random slopes for time will be added where supported by convergence and model fit. The primary contrasts of interest are: (1) group × condition × time for alpha power in predefined frontal and parietal regions of interest, and (2) condition × time and group × time interactions for cognitive and ASRS outcomes.

For EEG data, log-transformed alpha power (8-13 Hz) will be averaged within each region of interest and exposure phase. Within-subject change scores (T1-T0, and T9-T0 where applicable) will be analyzed in the LMM framework described above. Exploratory time-resolved effects across the 20-minute exposure will be examined using cluster-based permutation tests on epoch-wise alpha power, with family-wise error controlled at 0.05. Effect sizes will be reported as Cohen *d* for pairwise contrasts and partial eta squared (η^2^_p_) for omnibus tests.

Secondary outcomes include trajectories of emotional well-being assessed via weekly EMA, clinical functioning in the group with ADHD (ACOS-Self), quality of life (AAQoL), and nature connectedness (NCI). EMA scores over T0-T9 will be modeled with LMMs including fixed effects for time (treated as a continuous or categorical variable depending on fit), condition, group, and their interactions, with random intercepts for participants. ACOS-Self, AAQoL, and NCI change from T0 to T9 will be analyzed using separate LMMs with fixed effects for group, condition, and their interaction. Self-reported real-world nature and VR exposure during follow-up will be explored as time-varying covariates in additional models to probe their contribution to decay or maintenance of effects.

To incorporate a dimensional perspective, *z*-scored ASRS total and subscale scores will be included as continuous predictors in a restricted set of prespecified models [85] (eg, ASRS × condition × time interactions for alpha power and cognitive outcomes). These analyses will test whether attentional trait variation predicts sensitivity to environmental exposure across the full sample, without overparameterizing models.

Multiple-comparison control will be applied at the level of outcome families: EEG (regions of interest and key contrasts), cognitive tasks (Meta Mind and Star Racer indices), EMA trajectories, and clinical measures. Within each family, *P* values will be adjusted using false discovery rate procedures; unadjusted and adjusted values will both be reported.

Model assumptions (normality of residuals, homoscedasticity, and, where relevant, sphericity) will be checked using diagnostic plots and formal tests. If assumptions are violated, transformations or robust alternatives will be considered. Missing data will primarily be handled within the mixed-model framework under a missing-at-random assumption. In addition, sensitivity analyses will be conducted using multiple imputation and complete-case subsets (participants with data at least up to T1 and T9) to examine the impact of attrition on key inferences.

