This view aligns with dimensional frameworks such as the Research Domain Criteria [61], which emphasize the distributed neurobiological underpinnings of attentional and regulatory processes across clinical and nonclinical populations, and dual-pathway models that highlight heterogeneous cognitive and motivational routes to ADHD symptoms [62]. Studying ADHD-related traits along continuous spectra, rather than only using categorical diagnoses, allows us to examine whether variation in symptom levels is linked to variation in environmental sensitivity and restorative responses. From an ecological standpoint, comparing adults with ADHD and neurotypical controls in both real nature and VR nature settings provides a practical way to test how attentional and affective mechanisms operate in real-world-like environments. Natural settings may preferentially engage bottom-up sensory processing and low-effort neural restoration, whereas VR nature may rely more on cognitively engaged, top-down routes. By modeling ADHD symptom dimensions across the full sample and including diagnostic group, this study aims to characterize where responses to real and virtual nature converge and where they diverge and to identify conditions under which VR-based nature exposure is more or less suitable for individuals with higher ADHD traits.

The overarching aim of this study is to test whether immersive VR-simulated nature can approximate the cognitive and neural benefits of real-world nature and to identify for whom each modality is most suitable. To this end, we focus on 3 core questions. First, we ask whether a brief exposure to real and VR-simulated nature produces comparable immediate changes in attention, cognitive flexibility, affect, and EEG markers of restoration relative to baseline or control conditions. Second, we examine whether adults with ADHD differ from neurotypical adults in these cognitive, affective, and neural responses to real and virtual nature. Third, we investigate, across the full sample, how continuous ADHD symptom dimensions and related traits predict the magnitude and durability of benefits from each type of nature exposure.

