Based on the literature and the theoretical framework outlined above, we hypothesize that both real and VR-simulated nature will acutely improve attention, cognitive flexibility, and mood and will be accompanied by EEG changes consistent with restoration, but that real nature will show stronger signatures of low-effort, bottom-up restoration than VR. We further expect that adults with ADHD will show equal or greater cognitive and affective gains than neurotypical adults after both real and VR-simulated nature, while displaying distinct patterns of prefrontal and parietal EEG change, reflecting different regulatory mechanisms. More tentatively, we anticipate that individual differences in ADHD-related symptoms will shape both the size and the time course of these effects: higher symptom levels may be linked to larger immediate benefits from nature exposure, but also to a faster decline of gains over the follow-up period, and the pattern of attenuation may differ between real and virtual nature along the continuum from neurotypical adults to those with more pronounced ADHD traits. Together, these aims position the study to clarify where responses to real and virtual nature converge, where they diverge, and under which conditions VR-based nature exposure is a suitable supplement to real-world nature for adults with higher ADHD traits.

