#### Power

Sample size estimation focused on the primary mechanistic outcomes of the study, namely preexposure to postexposure changes in EEG alpha power and performance on the 2 cognitive tasks as a function of diagnostic group (ADHD vs neurotypical) and exposure condition (real nature vs VR nature). Power calculations were conducted in G*Power (version 3.1; Heinrich Heine University Düsseldorf), using a 2 × 2 × 2 mixed-model ANOVA (group × condition × time: preexposure vs postexposure). Pilot data from a comparable ADHD sample [84] indicated a pre-to-post change in alpha amplitude of 6.93 μV (SD 2.04) at baseline and 7.88 μV (SD 1.83) postintervention, corresponding to a Cohen *d* of 0.49 (moderate effect size) for the within-subject contrast. Assuming a correlation of 0.5 among repeated measures, this maps onto a repeated-measures ANOVA effect size in the moderate range.

Using a 2-tailed α of .05 and desired power of 0.80, the required total sample size was calculated to be 64 to 72 participants (approximately 16 to 18 per cell in the 2 × 2 design) to detect effects in this range on the primary EEG outcome. To accommodate potential attrition and data loss (eg, unusable EEG recordings), a 20% buffer was applied, resulting in a final recruitment target of 80 participants (n=20 per subgroup). This sample size is expected to provide adequate statistical power to detect moderate pre-post effects and group × condition interactions on alpha power and core cognitive outcomes.

Secondary and exploratory analyses (eg, EMA trajectories, dimensional ASRS scores, and follow-up data) will be modeled using linear mixed-effects approaches in the same sample. These models are intended to characterize patterns of change over time and symptom-related gradients in responsiveness; findings from these analyses will therefore be interpreted with appropriate attention to effect sizes and precision estimates rather than relying solely on hypothesis-testing thresholds. The planned sample provides ≥80% power to detect moderate pre-post changes in alpha power for the primary group × condition × time effect in the planned linear mixed-effects analysis. Analyses of higher-order interactions and secondary outcomes (eg, EMA trajectories) will be considered exploratory and interpreted cautiously.

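### For EEG alpha, the only contrast named primary is group × condition × time; the real-versus-VR contrast that the first hypothesis needs is fitted but not named primary, and the power claim does not support either interaction

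*Protocol article*

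**What the plan says.** The Introduction puts the modality comparison first. The first core question asks "whether a brief exposure to real and VR-simulated nature produces comparable immediate changes in attention, cognitive flexibility, affect, and EEG markers of restoration". The matching hypothesis is that both exposures help but that "real nature will show stronger signatures of low-effort, bottom-up restoration than VR".

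Statistical Methods specifies a mixed model with condition, group, time and their interactions, and then lists the primary contrasts. For alpha there is one: "group × condition × time for alpha power in predefined frontal and parietal regions of interest". The two-way terms appear in the second item, which is limited to other outcomes: "condition × time and group × time interactions for cognitive and ASRS outcomes".

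The Power section says: "The planned sample provides ≥80% power to detect moderate pre-post changes in alpha power for the primary group × condition × time effect". Its next sentence reads: "Analyses of higher-order interactions and secondary outcomes (eg, EMA trajectories) will be considered exploratory and interpreted cautiously". The effect size behind the calculation is a pilot pre-to-post change in alpha amplitude.

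**The concern.** Whether EEG restoration is stronger after real than after VR nature is a question about condition × time. Group × condition × time asks something else: whether the real-VR difference is larger in one diagnostic group than in the other. The two can diverge completely. If real nature raises alpha more than VR by the same amount in adults with and without ADHD, the three-way term is exactly zero.

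The comparative part of the first hypothesis would then be true while the only EEG contrast named primary would be expected to come out null. The result that answers the question would carry no primary label, and promoting it after seeing the data would be a post hoc change. The choice also affects the adjusted P values, because false discovery rate control in the EEG family runs over regions and key contrasts. Condition is the only randomised factor, so the contrast left without the label is the randomised comparison itself.

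**Working it through.** **Inputs (Power section).** Baseline 6.93 μV (SD 2.04); post 7.88 μV (SD 1.83); correlation 0.5; two-sided α 0.05; power 0.80; 80 participants, 20 per cell.

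**The plan's own figures.**
- Change = 7.88 − 6.93 = 0.95 μV. Averaged SD = √((2.04² + 1.83²)/2) = 1.938. d = 0.95/1.938 = 0.490. The stated d reproduces.
- SD of change = √(2.04² + 1.83² − 2 × 0.5 × 2.04 × 1.83) = 1.944, so the standardised change is 0.95/1.944 = 0.489.
- The required 64 to 72 does not reproduce from this d. With f = d/2 = 0.245, the repeated-measures within-between calculation gives N = 50 (3 df) or 35 (1 df). An unstated f of about 0.20 to 0.21 with 3 df gives 73 to 66. The target of 80 equals 64/(1 − 0.20); 72 would give 90.

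**Which effect d = 0.49 describes.** It is one group's change over time. It is neither a difference between arms in change nor a difference between diagnostic groups in that difference.

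**Standard errors, in change-score SD units, 20 per cell.**
- Time: √(1/80) = 0.112.
- Condition × time (real minus VR, averaged over groups): √(1/40 + 1/40) = 0.224.
- Group × condition × time (difference of the two real-minus-VR differences): √(4/20) = 0.447.

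**Smallest effect detectable at 80% power, 2.80 × SE.**
- Condition × time: 2.80 × 0.224 = 0.63 SD.
- Three-way: 2.80 × 0.447 = 1.25 SD.
- At 16 per cell, after the planned 20% loss: 0.70 and 1.40 SD.

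**Power if 0.95 μV (0.49 SD) is taken as the size of each effect (noncentral t).** The documents give no size for either interaction, so this is an assumption for those two rows.

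| Effect | N = 80 | N = 64 |
|---|---|---|
| Time | 0.99 | 0.97 |
| Condition × time | 0.58 | 0.49 |
| Group × condition × time | 0.19 | 0.16 |

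At half that size (0.475 μV) and N = 80, condition × time has power 0.19 and the three-way term 0.08. At double that size the three-way term has power 0.58. To reach 80% at 0.95 μV, condition × time needs 66 per arm (132 in total) and the three-way term about 526 in total.

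**What the named primary test does when the first hypothesis is true.** In 20,000 simulated trials with 20 per cell and real better than VR by 0.95 μV in both groups, condition × time rejected in 58% of runs and the three-way term in 5.1%. The second figure is its type I error and would not change with the size of a common real-VR difference.

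**The case against.** Three stronger readings are tempting, and the documents do not support them.

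1. *A reader might infer that real versus VR on EEG goes untested.* It does not. Condition × time is part of the prespecified alpha model and will be estimated. The multiplicity paragraph speaks of key EEG contrasts in the plural, so more than one may be intended. What is missing is the primary label.

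2. *A reader might infer that the three-way term is off target and should be demoted.* It bears directly on the second core question, on the aim of identifying for whom each modality suits, and on the prediction of distinct EEG patterns in ADHD. Keeping it as primary is the sponsor's choice; adding condition × time closes the gap without removing it.

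3. *A reader might infer a flat contradiction between primary and exploratory.* The exploratory sentence does not name the three-way term, and the sentence before it calls that term primary. Higher-order could mean the models with T9 or with ASRS as a continuous predictor. Still, the three-way term is the highest-order term of the T0-T1 model, and the text does not exempt it. The ambiguity stands.

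Two further points are fair. The 5% figure only restates that a true null rejects at α; its use is to show that the two contrasts answer different questions. And condition × time covers only the comparative part of the first hypothesis; improvement after both exposures is a time effect.

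What survives all this: the list of primary contrasts is an explicit choice, it gives condition × time to the cognitive and ASRS outcomes but not to alpha, and the power claim is attached to an effect that its inputs do not describe.

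**Conclusion.** The point holds as a gap in labelling together with an unsupported power statement. The only alpha contrast named primary does not test whether real nature restores more than VR, and a difference shared by both diagnostic groups leaves it at its 5% error rate. The status of the three-way term is ambiguous in the Power section.

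The claim of at least 80% power is supported by d = 0.49 only for the time effect (0.99 at N = 80). For the three-way term, 80% power needs about 1.25 change-score SD; for condition × time, about 0.63 SD.

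These sizes assume 20 analysable participants per cell, equal variances and an unadjusted two-sided α of 0.05; losses or false discovery rate adjustment would make them less favourable. The 0.58 and 0.19 also assume that 0.49 SD applies to the interactions, and that the pilot's amplitude in μV carries over to the log-transformed power to be analysed. The labelling point depends on none of these figures.

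**What to change.** In Statistical Methods, add condition × time (T1 versus T0, averaged over the diagnostic strata) as a primary contrast for alpha in the predefined frontal and parietal regions, and add group × time for the second core question. State once, with the same wording in Power and Statistical Methods, whether group × condition × time is primary or exploratory. List the named contrasts as members of the EEG false discovery rate family.

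In Power, replace the claim of at least 80% for the three-way effect. Deleting the word primary there would leave the untenable figure in place. State that d = 0.49 is a pre-post effect, and give for each named contrast either the detectable size (about 0.63 and 1.25 SD at 20 per cell) or the power at a justified interaction size.

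Cost: the same model supplies every contrast, so the change is wording in the protocol and the registrations plus a redone power statement. The downsides are one or two more contrasts in the EEG family and a less favourable power statement. It should be made before outcome data exist; the article expects data collection to start in April 2026.

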### Study Design

This study uses a randomized experimental design with a between-subjects factor and a within-subject repeated-measures component over an 8-week follow-up period. Participants will be randomly assigned to 1 of 2 exposure conditions: a real natural environment or an immersive VR-simulated natural environment. Cognitive performance, emotional well-being, nature connectedness, and ADHD symptomatology will be assessed both before and immediately after exposure, with additional follow-up assessments conducted over the next 8 weeks, while brain activity will be continuously recorded during the exposure session.

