### Procedures

Participant enrollment will be conducted through a face-to-face clinical interview with a trained psychologist or psychiatrist to confirm the diagnosis of ADHD and assess potential comorbidities based on *DSM-5* (*Diagnostic and Statistical Manual of Mental Disorders, Fifth Edition*) criteria.

Following informed consent and completion of baseline assessments, participants will be stratified by diagnostic status (ADHD vs neurotypical control). Within each stratum, the random allocation sequence will be generated by an independent research coordinator (not involved in recruitment or outcome assessment) using computer-generated permuted blocks of variable size with a 1:1 allocation ratio. This stratified block design ensures balanced group sizes over time and equal distribution of diagnostic groups across conditions.

The allocation sequence will be implemented using sequentially numbered, opaque, sealed envelopes prepared in advance by the independent research coordinator. Treating clinicians or research assistants will enroll participants and open the next envelope only after baseline measures are completed, ensuring that upcoming assignments remain concealed from both participants and enrollment staff. Due to the nature of the intervention condition, blinding of participants and experimenters is not feasible; however, data analysts will remain blinded to group allocation and condition labels until the primary analyses are completed to minimize bias during statistical analysis.

As illustrated in Figure 1, cognitive and emotional assessments will be administered at 10 time points: preexposure (T0), immediately postexposure (T1), and weekly over an 8-week follow-up period (T2-T9). These assessments will be completed online within the study platform. ADHD-specific assessments will be conducted at 3 time points: T0, T1, and the final follow-up (T9). EEG data will be recorded continuously during the exposure session to capture real-time brain activity in response to the environmental condition.

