#### Exposure Duration

Both exposure conditions use a fixed 20-minute session. This duration was selected to balance efficacy and tolerability, particularly for adults with ADHD. From a safety perspective, a review of temporal aspects of simulator sickness indicates that longer VR exposure is one of the strongest predictors of cybersickness, with more severe symptoms often emerging after approximately 20 to 30 minutes of continuous use [68]. In parallel, work on VR applications for individuals with attentional difficulties suggests that prolonged continuous tasks can lead to vigilance decrement, frustration, and disengagement in people with ADHD [69]. Keeping the exposure at 20 minutes therefore provides a conservative upper bound that aims to minimize the risk of sensory overload and cybersickness while maintaining engagement, especially in the group with ADHD.

At the same time, 20 minutes is sufficient to capture meaningful restorative effects. Although dose-response data for EEG in natural environments are limited, field studies of nature exposure in daily life have shown that approximately 20 minutes in urban green spaces can already produce measurable changes in stress-related biomarkers and autonomic regulation [70]. Given that EEG indexes neural activity on a millisecond timescale, a 20-minute window is expected to provide ample data to observe changes in cognitive processing and brain dynamics during exposure without extending into durations where fatigue and simulator sickness become more common. Taken together, a 20-minute session was judged to offer an adequate “dose” to elicit and measure neural and cognitive responses to real and VR-simulated nature while reducing the likelihood of adverse effects and dropout, particularly among adults with ADHD.

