In parallel, the integration of mobile EEG in both real and VR settings is intended to provide converging neurophysiological evidence on attentional engagement restoration. Alpha power and related spectral measures will be examined alongside behavioral and self-report outcomes, with the aim of identifying neural signatures that correspond to subjective restoration or cognitive effort. Although the EMOTIV FLEX system offers only moderate spatial resolution compared with laboratory-based EEG, its portability enables ecologically valid recording during naturalistic exposure, which is central to the aims of this protocol.

Several limitations should be acknowledged. The study compares real nature with VR-simulated nature but does not include a nonnature digital control condition, which limits inferences about whether observed effects are specific to natural content vs immersion or digital engagement more broadly. Individual differences in sensory sensitivity and simulator sickness may affect responses to the VR condition despite screening, safety monitoring, and the use of a relatively short (20-minute) exposure. EEG collected during movement-constrained outdoor and VR sessions will still be susceptible to muscle and motion artifacts, and results will depend on rigorous preprocessing and conservative quality control. Conducting the real-nature condition outdoors inevitably introduces variability in weather, temperature, light, ambient noise, and unexpected stimuli. To limit extreme discrepancies, data collection will be scheduled within months of relatively stable weather, sessions will be arranged flexibly to avoid adverse conditions, and key environmental characteristics (eg, temperature, wind, noise level, and light intensity) will be logged to support transparent reporting and exploratory adjustment. In addition, although dimensional modeling improves ecological and theoretical validity, estimates of interaction effects may be constrained by the planned sample size and by measurement noise in self-report data.

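### Group × time on the cognitive games mixes any ADHD–control difference in retest learning and visit fatigue with a difference in response to nature, so it cannot be reported as the latter

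*Protocol article*

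**What the plan says.** All places are in the protocol article.

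- **Contrasts (Statistical Methods).** The primary contrasts for cognition are "condition × time and group × time interactions for cognitive and ASRS outcomes". Group × condition × time is named as primary only for alpha power.
- **Arms (Study Design).** Participants are randomised to "a real natural environment or an immersive VR-simulated natural environment". Both are nature exposures.
- **Diagnosis (Procedures).** ADHD versus neurotypical is a stratification factor. Only the exposure condition is randomised, within each stratum.
- **Timing (Procedures).** The "cognitive and emotional assessments will be administered at 10 time points", the first two being immediately before and immediately after exposure (T0 and T1). T0 takes 30 to 40 minutes and the exposure is a 20-minute seated session. T1 takes a further 20 to 30 minutes.
- **Question and hypothesis (end of the Introduction).** The second core question asks whether the two groups differ in their cognitive, affective and neural responses to real and virtual nature. The matching hypothesis is that "adults with ADHD will show equal or greater cognitive and affective gains than neurotypical adults after both real and VR-simulated nature".
- **Limitation conceded (Discussion).** The study "does not include a nonnature digital control condition". The stated consequence is uncertainty about natural content as against immersion or digital engagement.

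**The concern.** Each group's change on a game from T0 to T1 has several sources: the exposure, having played the game before, and tiredness built up over the visit. Randomisation balances the last two between the real and VR arms in expectation. It does nothing to balance them between adults with ADHD and controls, because diagnosis is a characteristic that participants bring with them. No group of either diagnosis repeats the games without a nature exposure, so the data hold no estimate of the retest and fatigue part on its own.

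At stake is the cognitive answer to the second core question. A steeper learning curve in the ADHD group would look like the predicted greater gain. Earlier fatigue in that group would hide a real gain or look like a smaller one. Either could happen if nature did nothing in anyone.

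**Working it through.** **Inputs.** From the Power section: 80 participants, 20 per cell, so 40 per diagnostic group; two-sided α of 0.05; correlation r = 0.5 between repeated measures; a 20% allowance for loss, which leaves 32 per group. The value r = 0.5 is introduced there alongside alpha amplitude, so using it for the games is an assumption. The size of the group difference in retest and fatigue change, δ, is not in the documents and is assumed over a range.

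**The plan's own figure.** The plan gives none for this contrast. Its nearest figure is the within-subject effect size, which reproduces: (7.88 − 6.93) / √((2.04² + 1.83²)/2) = 0.95/1.938 = 0.49. It concerns alpha amplitude and does not bear on what follows.

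**What group × time estimates.** Write N for the nature effect averaged over the two arms and L for the retest and fatigue change, with subscripts A (ADHD) and C (control):

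group × time = (N_A + L_A) − (N_C + L_C) = (N_A − N_C) + (L_A − L_C)

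Only the sum is observed. More participants narrow the interval around the sum and leave δ = L_A − L_C inside it.

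**The other contrasts.** In condition × time, the part of L common to both arms cancels. In group × condition × time, (real − VR change in ADHD) − (real − VR change in controls), it cancels too. That last contrast answers a different question, however. If controls gain g in each arm and ADHD participants gain 2g in each arm, it equals (2g − 2g) − (g − g) = 0, although the ADHD group has gained twice as much.

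**Size, with no nature effect in either group.** In baseline SD units, the SD of a change score is √(2(1 − r)), which is 1 at r = 0.5 and √0.6 = 0.775 at r = 0.7. The standard error of group × time is that SD × √(2/n), with n per group. The chance of a significant result comes from the noncentral t distribution with 2n − 2 degrees of freedom and noncentrality δ/SE.

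| Setting | SE | δ = 0.2 | δ = 0.3 | δ = 0.5 |
|---|---|---|---|---|
| r = 0.5, n = 40 | 0.224 | 14% | 26% | 60% |
| r = 0.5, n = 32 | 0.250 | 12% | 22% | 50% |
| r = 0.7, n = 40 | 0.173 | 21% | 40% | 81% |

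At δ = 0 every row gives 5%. Simulating 20,000 trials at 20 per cell and r = 0.5 gave 14%, 26% and 60% for group × time, with its mean estimate shifted by δ. In the same simulations condition × time and group × condition × time stayed between 4.7% and 5.2%.

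**Power of the three-way contrast.** At 20 per cell and r = 0.5 its standard error is 1 × √(4/20) = 0.447. The difference detectable with 80% power is about (1.96 + 0.84) × 0.447 = 1.25 SD. At r = 0.7 it is 0.97 SD.

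**The case against.** The strongest reply is that the rates are hypothetical. They are the power of a t test at differences that no document supports. They are per test, before the planned false discovery rate adjustment within the cognitive family, and the 40-per-group rows assume no loss. All of this stands. The figures show how sensitive the contrast is and do not forecast an error rate. The identification argument does not depend on them.

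Four stronger readings are tempting, and the documents do not support them:

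- *The protocol itself says ADHD participants tire sooner than controls.* The Exposure Duration section says that "prolonged continuous tasks can lead to vigilance decrement, frustration, and disengagement in people with ADHD". It is speaking of VR applications, makes no comparison with controls, and is justifying a short exposure. It makes a group difference plausible and no more.
- *The whole second core question rests on this contrast.* That question also covers affect, which is modelled through the momentary assessments, and neural response, for which the primary contrast is the three-way one. Only the cognitive part rests on group × time.
- *The plan has no practice run.* The article gives each game a single sentence. Practice trials and alternate forms may well be in the full protocol, so silence here is not evidence.
- *Learning and fatigue are identical in the two arms.* Only the part common to both arms cancels. Fatigue could differ between a worn headset and a forest seat, and T1 is completed outdoors in the real-nature arm.

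It may also be said that the limitations paragraph already covers the point. It does so only in part. It warns about natural content as against immersion or digital engagement; it does not mention group-specific retest or fatigue change, nor limit what group × time may show.

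**Conclusion.** The point holds for Meta Mind and Star Racer. Group × time is the only primary cognitive contrast that involves diagnosis, and it cannot separate a group difference in response to nature from a group difference in retest learning and fatigue, at any sample size. This follows from three features of the design: both arms receive nature, diagnosis is not randomised, and the games are repeated within one visit.

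The bias equals the retest and fatigue difference itself and can run in either direction. Its size is unknown. Under the stated assumptions, differences of 0.2 to 0.5 SD would raise the 5% rate of a single unadjusted test to roughly 14% to 60% with 40 per group, or 12% to 50% with 32.

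A reader might infer that group × condition × time could take over the claim that ADHD participants respond more or less to nature. It cannot: it addresses only whether the real-versus-VR difference depends on diagnosis. Condition × time is not affected by a group difference in retest or fatigue that is the same in both arms.

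**What to change.** 1. In Statistical Methods, state that group × time for the games is a descriptive difference in pre-post change between diagnostic groups, that it includes retest and fatigue effects, and that it will not be reported as a differential response to nature. Bring the second core question and its hypothesis in the Introduction into line for the cognitive outcomes.
2. Report group × condition × time for the games beside it. State that it tests only whether the real-versus-VR difference depends on diagnosis, that retest and fatigue change common to both arms cancels in it, that it does not show whether ADHD participants respond more or less to nature overall, and that power is low at 20 per cell (80% only near 1.25 SD at r = 0.5).
3. Optionally, if the full protocol has none, add a short unscored familiarisation run of each game before the scored T0 run. This reduces early learning but not fatigue, and it does not make group × time identifiable.

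The first two items cost some wording and a narrower claim; the three-way term is already in the fitted model. The third lengthens T0 slightly.
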